### 6.4 Exclusion Criteria

- Acute cardiopulmonary diseases, i.e. pneumonia, bronchial asthma, heart attack, occurred within 4 weeks prior to study admission, etc.
- Instable fractures or decubiti on trunk and lower extremities
- Severe osteoporosis of the lower extremities
- Severe contractures of hip and knee
- Severe spasticity
- Pacemaker
- Pregnancy
- Leg length (heel to trochanter major)  $> 100$  cm or  $< 70$  cm.

## 7 Study procedure

### 7.1 Procedure

| Erigo                                                                                                                                                                                           | Tilt table |
|-------------------------------------------------------------------------------------------------------------------------------------------------------------------------------------------------|------------|
| Attachment of ECG electrodes, blood pressure cuff, and pulsoxymeter for continuous measurement of pulse, ECG, blood pressure, and oxygen saturation; also for performance of first measurement. |            |
| Patient is transferred from bed/wheelchair to the Erigo or to the tilt table, is attached to it, and secured with a belt over the stomach.                                                      |            |

|                                                                                                                                                                                                                                                                                                |  |
|------------------------------------------------------------------------------------------------------------------------------------------------------------------------------------------------------------------------------------------------------------------------------------------------|--|
| The foot supports are adjusted to the individual length of the legs of the patients.                                                                                                                                                                                                           |  |
| Adjustment of range of leg movement to patient's maximally possible range.                                                                                                                                                                                                                     |  |
| Start of leg drive at a maximally tolerated speed (the goal is 40 steps/min or at least 20 steps/min) while patient remains in horizontal position.                                                                                                                                            |  |
| Upright placement to 30 degrees; conditions maintained for about 5 min.                                                                                                                                                                                                                        |  |
| Subsequently the patient is uprighted to 50 degrees (if appropriate, with same drive parameters); if circulation is good, to 70 degrees.                                                                                                                                                       |  |
| At least 15-min-long or maximally 30-min-long therapy during the achieved angle of verticality. The duration of mobilization in the indicated time period is as long as possible, if there is no depression of the circulation and in agreement with the predetermined criteria (see below).   |  |
| At the end of therapy the Erigo or tilt table is lowered into the initial horizontal position by about 15 degrees, with a break for the patient to acclimatize him/herself. After the final measurement the apparatus is disassembled and the patient is transferred to the bed or wheelchair. |  |

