#### 4.2.2 Secondary outcome measure

To evaluate an immediate stabilizing effect of the Erigo therapy on circulation, the following cardiovascular parameters will be measured:

- Heart rate
- Blood pressure; the Hypothesis: difference between initial value and the value after the intervention phase is greater for the tilt-table therapy (drop in blood pressure during tilt-table therapy)
- Oxygen saturation; the Hypothesis: increased oxygen saturation during Erigo therapy
- As co-variables the duration of verticalization (max. of 30 min per therapy session), and the degree of the maximum tilt will be analyzed

To evaluate a clinically unapparent effect on vigilance the following parameters will be measured:

- Skin conductance as reaction to command (should increase during Erigo therapy)
- Heart rate variability (should increase during Erigo therapy)
- Head control/movement during therapy (better during Erigo therapy)

The change in muscle tone or spasticity will be measured before the intervention, after the intervention, and after a 3 week follow-up period using the

- Ashworth-Scala.

To better compare the results of this study with results of international studies, the following parameters will be measured:

- at study onset: GCS (Glasgow Coma Scale)
- at discharge: GOS (Glasgow Outcome Scale)

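### Followed in row order, the section 7.1 table takes the first circulatory reading before the transfer, in bed or wheelchair, but the final one horizontal on the device, so the blood-pressure change may carry an uncontrolled posture difference.

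*Protocol*

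**What the plan says.** The procedure table in Protocol section 7.1 lists the steps of a session for both devices.

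- **First row.** ECG electrodes, cuff and pulse oximeter are attached "for continuous measurement of pulse, ECG, blood pressure, and oxygen saturation; also for performance of first measurement".
- **Second row.** "Patient is transferred from bed/wheelchair to the Erigo or to the tilt table, is attached to it, and secured with a belt over the stomach".
- **Leg drive (Erigo).** A horizontal position on the device first appears here: the drive starts "while patient remains in horizontal position". No reading is tied to this moment.
- **Last row.** The device "is lowered into the initial horizontal position by about 15 degrees, with a break for the patient to acclimatize him/herself". Then: "After the final measurement the apparatus is disassembled and the patient is transferred to the bed or wheelchair".

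Section 4.2.2 lists heart rate, blood pressure and oxygen saturation as secondary circulatory outcomes. Its blood-pressure hypothesis is that the "difference between initial value and the value after the intervention phase is greater for the tilt-table therapy", with a bracketed remark about a fall in pressure during tilt-table therapy. The schedule in section 7.5 places blood pressure and heart rate during each therapy and gives no separate time point for a starting value.

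**The concern.** A change score is only as good as its starting value. Here the end reading has a fixed posture and a settling period, and the start reading has neither. The protocol itself gives reason to think that posture matters in these patients. Section 3 says that in the early phase even sitting is often hard to achieve because of circulation problems. Section 5.3 notes that orthostatic syncope can occur during the move to the wheelchair. Lying and sitting pressures should therefore not be treated as interchangeable.

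Two consequences follow if the first measurement is the initial value:

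- **Noise.** A mix of bed and wheelchair starts adds variation that has nothing to do with the device.
- **Possible bias at later sessions.** Starting posture after the first session is a post-randomization variable. Section 3 connects circulatory adaptation with tolerating the wheelchair for longer, and expects patients on the Erigo to be mobilized sooner. If that changed how patients arrive, the arms could start from different mixes of posture.

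The secondary circulatory comparison is at stake, not the primary outcome.

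**Working it through.** The protocol gives no blood-pressure SD, no postural difference and no share of wheelchair starts. There is therefore no figure of its own to reproduce on this point. The sample size in section 6.2.2 (22 per group, 25 with 10% drop-out) rests on the CRS alone and does not enter.

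**Step 1: compare the two readings in 7.1.**

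| | First measurement | Final measurement |
|---|---|---|
| Place in the table | At sensor attachment, one row before the transfer | After lowering, before the transfer back |
| Posture | Not fixed: bed or wheelchair | Horizontal on the device |
| Settling period | None stated | A break is stated |

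No section fixes the posture at the first reading or asks for it to be recorded.

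**Step 2: write the change as a formula.** Let d be lying minus sitting systolic pressure before the session. For a bed start, drop = lying value − final value. For a wheelchair start, drop = (lying value − d) − final value. The wheelchair start therefore shows a drop smaller by d, whatever happened on the device. The same holds if the comparison value is read while tilted, because the initial value is the same.

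**Step 3: added noise.** With a share p of wheelchair starts, posture adds SD = d × √(p(1 − p)) to the initial reading. Both d and p are assumptions.

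| d (mmHg) | p = 0.1 (factor 0.3) | p = 0.5 (factor 0.5) |
|---|---|---|
| 5 | 1.5 | 2.5 |
| 10 | 3.0 | 5.0 |
| 15 | 4.5 | 7.5 |

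This cannot be turned into a loss of power without a blood-pressure SD.

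**Step 4: possible bias.** If the arms differ by Δp in the share of wheelchair starts, the contrast shifts by d × Δp, towards a smaller drop in the arm with more wheelchair starts. Both inputs are again assumptions.

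| d (mmHg) | Δp = 0 | 0.1 | 0.2 | 0.4 |
|---|---|---|---|---|
| 5 | 0 | 0.5 | 1 | 2 |
| 10 | 0 | 1 | 2 | 4 |
| 15 | 0 | 1.5 | 3 | 6 |

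**Step 5: when Δp could differ from zero.** At the first session randomization balances starting posture in expectation, so the expected Δp is 0. Section 6 plans four sessions a week for three weeks, 4 × 3 = 12 sessions. At the later ones Δp may move away from zero, but nothing in the protocol says that it will.

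**The case against.** **The timing is inferred.** The first row says what the sensors are for, not when or in what posture a reading is taken. That is fair. But the row precedes the transfer, and the last row mirrors it, with measurement first and transfer afterwards. Staff following the table would take the reading before the transfer.

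**The initial value is not tied to the first measurement.** Section 4.2.2 does not refer to 7.1, and 7.1 uses the word initial only for the horizontal position of the device. Monitoring is continuous, so a horizontal reading before tilt will exist, and an analysis plan could choose it. This stands as a limit: the link is the natural reading, not a stated one. It also makes the remedy easy. It does not make the written step order a good one, and without a record of starting posture no later analysis can adjust for it.

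**The hypothesis may compare values before and after the three weeks.** Section 4.2 uses the term intervention phase in that sense. If the initial value is a single pre-treatment reading, randomization balances its posture in expectation and only the noise remains. The bracketed remark in 4.2.2 points instead to a change within a session.

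**A bias in favour of the Erigo is speculative.** A reader might infer that Erigo patients will reach the wheelchair sooner and so show falsely small drops. The documents do not support that as a finding. They do not say what decides a bed or wheelchair start, which could be ward scheduling. The mechanism also needs the Erigo to have improved circulation or mobilization already; without such an effect it gives no imbalance. And patients adapted enough to use a wheelchair may have a smaller postural difference. All of this stands.

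**Conclusion.** The point holds as a weakness in how the starting value is measured. Followed as written, the two readings that 4.2.2 would most naturally pair do not share a defined posture, so the change in blood pressure, and likewise in heart rate, includes an uncontrolled posture difference. This rests on reading the 7.1 table in row order and on taking its first measurement as the initial value.

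The sure consequence, if both bed and wheelchair starts occur and pressure differs between them, is noise: an SD of 1.5-7.5 mmHg per initial reading over the assumed range. A between-arm bias at later sessions is possible (0.5-6 mmHg for d of 5-15 mmHg and Δp of 0.1-0.4) but not shown. These figures only illustrate the formula; the true size cannot be derived from the protocol.

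Two further inferences should be avoided. The 20 mmHg fall in section 10 is a rule for stepping down the angle during uprighting, not a margin for this outcome, so the figures should not be scaled against it. And poor postural regulation is not an inclusion criterion in section 6.3; the protocol only describes it as frequent in the early phase.

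The primary CRS-R outcome and the sample size are untouched. This is a cheap improvement of minor severity.

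**What to change.** In section 7.1, place the reading that serves as the initial value after the transfer: patient horizontal and secured on the device, after a short rest of fixed length, before the leg drive starts (Erigo) and before any tilt (both arms). In section 4.2.2, define the initial value as this reading, with a reference to 7.1. Record for each session whether the patient came from bed or wheelchair. The pre-transfer reading may be kept for monitoring.

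The cost is one reordered table row, one recorded item and a few minutes of rest per session. Monitoring is already continuous, so no new equipment is needed.

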## 7.2 Pre-enrollment procedure

The CRS-R values will be obtained before enrollment. An ECG will be recorded if none is available. Additional invasive measures will not be taken.

## 7.3 Invasive measures

No invasive measures are scheduled within the scope of the study.

## 7.4 Non-invasive measures of pilot study

| Measures                                                                                  | Time point                                     | Period | Frequency |
|-------------------------------------------------------------------------------------------|------------------------------------------------|--------|-----------|
| Screening exam administered to determine eligibility, incl. use of patient medical record | pre enrollment                                 | 1 week | 1x        |
| ECG                                                                                       | pre enrollment                                 | 1 week | 1x        |
| ECG monitoring                                                                            | during each therapy session                    | 1 week | 2x        |
| Heart rate                                                                                | during each therapy session                    | 1 week | 2x        |
| Blood pressure                                                                            | during each therapy session                    | 1 week | 2x        |
| Oxygen saturation                                                                         | during each therapy session                    | 1 week | 2x        |
| Surface EMG                                                                               | during each therapy session                    | 1 week | 2x        |
| Skin conductance                                                                          | before and after each therapy session          | 1 week | 3x        |
| Heart rate variability                                                                    | before and after each therapy session          | 1 week | 3x        |
| Ashworth Scale                                                                            | before and after each therapy session          | 1 week | 2x        |
| Coma Recovery Scale-Revised                                                               | before, during, and after each therapy session | 1 week | 6x        |
| Glasgow Coma Scale                                                                        | at enrollment                                  | 1 week | 1x        |

## 7.5 Non-invasive measures of randomized controlled study

| Measures                                                                                  | Time point                                           | Period  | Frequency |
|-------------------------------------------------------------------------------------------|------------------------------------------------------|---------|-----------|
| Screening exam administered to determine eligibility, incl. use of patient medical record | pre enrollment                                       | 6 weeks | 1x        |
| ECG                                                                                       | pre enrollment                                       | 6 weeks | 1x        |
| ECG monitoring                                                                            | during each therapy                                  | 6 weeks | 9x        |
| Heart rate                                                                                | during each therapy                                  | 6 weeks | 9x        |
| Blood pressure                                                                            | during each therapy                                  | 6 weeks | 9x        |
| Oxygen saturation                                                                         | during each therapy                                  | 6 weeks | 9x        |
| Skin response                                                                             | before therapy, 3 and 6 weeks after start of therapy | 6 weeks | 3x        |
| Heart rate variability                                                                    | before therapy, 3 and 6 weeks after start of therapy | 6 weeks | 3x        |
| Ashworth Scale                                                                            | before therapy, 3 and 6 weeks after start of therapy | 6 weeks | 3x        |
| Coma Recovery Scale-R                                                                     | before therapy, 3 and 6 weeks after start of therapy | 6 weeks | 3x        |
| Glasgow Coma Scale                                                                        | before start of therapy                              | 6 weeks | 1x        |
| Glasgow Outcome Scale                                                                     | at hospital discharge                                |         | 1x        |

## 8 Concomittant drugs

Drug therapies for internistic, urological or other comorbidities are fully permitted with the exception of those cited in the conditions of the exclusion criteria (acute pneumonia, bronchial asthma). As regards co-occurring diseases, decisions will be made on an individual basis, which will be noted in the study protocol and its interpretation commented upon.

A drug therapy with the goal of increasing vigilance should not be started during the study. If such a therapy already began before the patient entered our clinic or before he/she was enrolled in the study, then no change in medication should be made during the course of the study. Since sufficient proof for the success of a drug-induced increase in vigilance has not been presented by current clinical studies despite good theoretical models ([8]), it is ethically justifiable to not begin such therapy during the duration of the study.

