### 9.3 Recording and reporting

#### 9.3.1 Recording an AE

Every AE must be documented in the report of adverse events.

In all cases the principal investigator must be clearly identified in the AE report. The report must be dated and signed by him/her. The report should moreover contain an evaluation of the causal connection between the event and the drug. The report form must be completed

The description of the AE includes the time of its occurrence, the duration, severity, intensity, outcome and the relationship to the study application and the necessary treatment. The principal investigator should estimate the intensity of every AE on the basis of the following classification:

- **Mild:** the symptom is clinically visible but the participant does not require treatment or intervention, and the symptom does not affect the participant's clinical status.
- **Moderate:** the participant is symptomatic and requires treatment because the symptom affects his/her clinical status.
- **Severe:** the participant is symptomatic and requires intensive treatment because the symptom significantly diminishes his/her clinical status.

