**Therapeutic consequences must be documented, for example drug treatment, exclusion from the study.**

An event is termed an “unexpected adverse event“ in connection with the tested medical product (MP) if its nature or severity does not agree with the known data on the safety and tolerance of the MP.

**Causality:** The following definitions are used to determine the connection between the use of a medical product (MP) and the AE:

- **Safe:** A reaction that follows within a reasonable temporal course after use of the test product, that follows a known or expected response pattern to the suspected test product, and disappears when removed or when the dosage is reduced and recurs with repeated exposure.
- **Probable:** A reaction that follows within a reasonable temporal course after use of the test product, that follows a known or expected response pattern to the suspected test product, and disappears when removed or when the dosage is reduced and cannot be explained by the known features of the patient’s clinical state.
- **Possible:** A reaction that follows within a reasonable temporal course after use of the test product, that follows a known or expected response pattern to the suspected test product, but which can be easily elicited by a number of other factors.
- **No connection:** A reaction for which there is sufficient information available to assume that there is no connection with the test product.
- **Unassessable:** It is not possible to assess a connection.

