## **10 Termination criteria**

Individual

- If the systolic blood pressure falls by 20 mmHg or the diastolic blood pressure by more than 10 mmHg during the uprighting of the patient, therapy is continued at the next lowest tolerated angle of uprightness (30 or 50 degrees).
- The same procedure is followed with symptoms of a presyncope (tachypnoe, paleness, increased sweating...).
- Therapy is immediately terminated if the pulse falls below 40 beats/min or rises above 140 beats/min.
- Arterial hypotension (<80 mmHg).
- The occurrence of a new disease or complication of the primary illness that makes a continuation of the study impossible.
- Legal proxy withdraws participation agreement.

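### Section 8 borrows an entry exclusion to limit drug treatment during the study, and this does not fit with the rules for co-occurring disease, adverse events and termination

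*Protocol*

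**What the plan says.** Protocol section 8 governs drugs taken during the study. Therapies for comorbidities are "fully permitted with the exception of those cited in the conditions of the exclusion criteria (acute pneumonia, bronchial asthma". The next sentence adds: "As regards co-occurring diseases, decisions will be made on an individual basis"; those decisions are to be noted and commented on.

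The criterion referred to is in section 6.4: "Acute cardiopulmonary diseases, i.e. pneumonia, bronchial asthma, heart attack, occurred within 4 weeks prior to study admission, etc". It applies at entry and lists diseases, not drugs.

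Two other sections deal with illness after entry. Section 9.3.1 grades an adverse event as moderate when "the participant is symptomatic and requires treatment because the symptom affects his/her clinical status", and requires: "Therapeutic consequences must be documented, for example drug treatment, exclusion from the study". Section 10 lists among the individual termination criteria: "The occurrence of a new disease or complication of the primary illness that makes a continuation of the study impossible".

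Section 6.1 has drop-outs replaced by the next patient, who takes over the drop-out's allocation. The rule is written for the pilot study, and the section says the study procedure is the same for the randomised trial.

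**The concern.** A condition for entering a trial and a rule on treatment within it do different jobs. Section 6.4 screens patients once. It cannot say anything about pneumonia that begins after randomisation. By pointing back to 6.4 for an exception to permitted drugs, section 8 makes the entry list do a job it was not written for.

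Two things are at stake. The first is safety. These patients cannot speak for themselves, and the sentence can be read as leaving treatment of a serious infection outside what the protocol allows. The second is the comparison of the arms. If a site resolves the uncertainty by taking a treated patient off study, that patient leaves for a reason arising after randomisation and may be replaced under 6.1. The protocol mentions intention-to-treat only as a log-book label for withdrawal at the caretaker's wish (6.2.2). It does not say that a patient removed because of illness or its treatment stays in follow-up.

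**Working it through.** The main check is textual: what each section says about a patient who becomes ill with pneumonia after randomisation.

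| Protocol section | What it governs | What it implies for this patient |
|---|---|---|
| 6.4 | Entry | Nothing; the patient has already been admitted |
| 8, exception | Drugs during the study | Drug treatment of pneumonia falls outside the permission |
| 8, next sentence | Co-occurring diseases | Case-by-case decision; not said whether it overrides the exception |
| 9.3.1 | Events during the study | Treatment is expected; drug treatment and exclusion are separate examples of consequences |
| 10 | Ending participation | The patient stays unless continuation is impossible; drugs are not mentioned |
| 6.1 | Drop-outs | Replacement, if the patient is counted as a drop-out |

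1. *What does the pronoun in the exception refer to?* It can mean the therapies or the comorbidities. If therapies, drugs for pneumonia and asthma are excepted. If comorbidities, drugs for those comorbidities are excepted. Read as a rule on drugs, the result is the same.

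2. *Can 6.4 supply a list of excepted drugs?* No. It names none.

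3. *Do the sections fit together for this patient?* Not on the literal reading. Under section 10 a patient who can continue stays in. Under 9.3.1 the event is treated and documented. Under the exception in section 8 that treatment lacks permission.

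4. *What does the 4-week window cover?* The wording of 6.4 allows it to attach to heart attack alone or to all the listed diseases. Only on the second reading could a patient with older asthma be admitted and then meet the exception in section 8.

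5. *Is there a number to reproduce?* No. The protocol gives no rate of pneumonia or asthma. For context, 6.2.2 requires 22 patients per group and enrols 25, so the margin is 50 − 2 × 22 = 6 patients. How much of it this wording could use up cannot be derived from the document.

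**The case against.** The strongest reply is that the sentence in section 8 only reminds the reader that patients with these diseases are not in the trial. The bracket names diseases, 6.4 names diseases, and the next sentence leaves co-occurring disease to individual decision. Section 9.3.1 plainly foresees drug treatment of illness on study. Taken as a whole, the protocol need not be read as forbidding anything. Much of this stands, and it rules out several stronger claims that a reader might infer:

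- *That the protocol bans treatment of pneumonia and asthma outright.* This follows only if the exception is read alone, without the next sentence and without 9.3.1.
- *That section 8 directly contradicts 6.4 and 10.* Section 6.4 governs entry and section 10 governs leaving. Neither says whether such drugs may be given. The conflict appears only when the literal reading is applied to a particular patient; the closest tension is with 9.3.1.
- *That the lists conflict because heart attack is in 6.4 but not in section 8.* The bracket may be a short pointer to a list that is itself open-ended.
- *That the arms would lose patients unequally because the device is expected to protect against pneumonia.* Section 5.2 attributes that effect to upright positioning, and both arms are tilted by the same procedure (7.1). A difference would need unequal verticalization in practice, which is not shown.
- *That a definite share of the sample is at risk.* Any pneumonia rate would be an unanchored assumption. Setting the number affected against the drop-out allowance would further assume that every affected patient is lost, which no section states.

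The benign reading still leaves a gap. Screening at entry cannot cover illness that starts later, and the sentence on individual decisions does not say what is decided or whether it overrides the exception.

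**Conclusion.** The concern holds as a defect of wording and consistency. Section 8 uses a list of diseases at admission to define an exception for drug treatment during the study. On its literal reading that exception does not fit with the rest of section 8, with 9.3.1 or with section 10. The reach of the 4-week window in 6.4 is a second, smaller ambiguity.

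The consequence is a risk, not a measured effect. It rests on the assumption that some site staff would follow the exception literally. The point shows no error in the sample size or in type I error, and no bias between the arms is demonstrated. It still deserves correction, because it touches patient safety and could lead to removal and replacement of patients after randomisation. Which clinical rule the sponsor intended cannot be settled from the document.

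**What to change.** 1. The sponsor and investigator should reconcile sections 6.4, 8, 9.3.1 and 10, so that the entry conditions, the rule on drugs during the study, the handling of adverse events and the termination criterion agree. The clinical content is theirs to decide.
2. In the same amendment, state which of the diseases in 6.4 the 4-week window applies to.
3. State that a patient who falls ill or receives such drugs after randomisation still has the week-3 and week-6 CRS-R already scheduled in 7.5, is analysed in the randomised group, and is not replaced as a drop-out under 6.1.

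The cost is a wording amendment and a slightly more heterogeneous group of patients in follow-up. No assessment is added to the schedule.
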